### Statistical Analysis

Demographic data for continuous variables will be presented as mean (SD), and categorical variables will be presented as count (percentage). Univariate analyses will be performed using *t* tests for independent groups for continuous variables and chi-square tests for categorical variables. Discriminations are assessed by plotting the receiver operating characteristic curve and calculating the area under the receiver operating characteristic curve (AUC) or *C* statistic. The accuracy of the prediction model will be analyzed using both Type I and Type II Parkes Error Grids. The sensitivity, specificity, and *F*_1_-score of the BGEM model will also be evaluated and presented to give a clear description of its strength and weakness.

The Parkes Error Grid is used to assess how clinically risky an inaccurate blood glucose reading might be. Each device reading is compared with a reference value and placed into 1 of 5 zones. Zone A means the reading is clinically accurate and would not change treatment. Zone B reflects small errors that might adjust a decision but have little or no impact on outcome. Zone C includes errors likely to affect clinical results. Zone D involves inaccuracies that could lead to clearly risky treatment decisions. Zone E represents dangerous errors that could cause severe or life-threatening consequences if acted upon [27].

The ML model will be trained using Lasso regression, cross-validation, and other ML techniques to find the optimal regularization parameter to ensure that the model generalizes to unseen data. The dataset is initially divided into a training set and a validation set. The training set is used for model development and hyperparameter tuning, while the validation set is reserved for a final, unbiased evaluation of the model’s performance. Analysis will ensure that the model does not overfit to the training data and is able to predict outcomes on new data with confidence. Once the optimal regularization parameter is identified through cross-validation, a final regression model is trained on the entire training set using this optimal regularization parameter value.

The blood sugar profiles of subjects with varying demographic characteristics will be analyzed and compared statistically to quantify the similarities and differences between individuals. Profile analysis and correlation and regression techniques will be used for the comparison of the blood sugar profiles, taking into consideration the correlation between the repeated measurements within each individual. Trending analysis will also be performed using mixed effects models and clustering methods, so as to incorporate the correlated repeated measurements at the 4 time points for each participant.

The data will be analyzed using statistical packages, including Stata (version 19) and ML packages R and Python. *P* values <.05 will be considered as statistically significant.

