**Objective:**

The aim of this study is to collect a large and more diverse dataset for the training of BGEM machine learning models. This dataset is intended to improve the model’s generalizability and to evaluate its performance across different age groups, racial groups, and skin types, with the goal of enhancing accuracy and robustness for diabetes risk assessment and glucose monitoring.

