### Model Training

During model training, 10-fold cross-validation was applied to obtain a robust estimate of generalization performance and to monitor potential overfitting. To prevent data leakage, particularly biometric identity-related features potentially embedded in the photoplethysmography data [26], we ensured that fragments from the same participant were not included in both the training and validation sets. Data collected in this clinical trial were used exclusively for model training and validation.

Additionally, given that this study employs short-term, mealtime prospective measurements of blood glucose profiles, we aim to leverage each participant’s individual blood glucose fluctuation pattern to explore prediction of diabetes risk or glucose levels and probable glycemia monitoring post meal. To achieve this, the photoplethysmography data from the 4 mealtime points for each participant will be combined into a time series, which will serve as input to a model trained to predict glucose levels or diabetes risk across all 4 points of the meal cycle. This approach allows the longitudinal aspect of the data—the participant-specific fluctuation pattern—to be fully utilized, potentially improving model performance and predictive accuracy.

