## Results

The IRB approval was given on July 15, 2024, after which the data collection was started on July 30, 2024, and finished on October 5, 2024; the analysis was projected to be concluded in the third quarter of 2025 and the results submitted for publication at the end of 2025.

A total of 885 participants (473 with diabetes and 412 without diabetes) were enrolled. Eight photoplethysmography recordings per participant were collected across 4 mealtime points using 2 wearable devices. Participants completed the International Physical Activity Questionnaire (IPAQ) long form and additional questionnaires on diabetes and related risk factors. Capillary and plasma blood tests were performed, and results were recorded.

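### The stated accuracy measures score single readings, so they cannot show whether the model follows an individual's glucose after a meal

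*Protocol article*

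**What the plan says.** **Goal.** The Objective in the Abstract describes the dataset as collected "with the goal of enhancing accuracy and robustness for diabetes risk assessment and glucose monitoring", and the last paragraph of the Introduction repeats both purposes. Model Training says why repeated readings were taken: "we aim to leverage each participant’s individual blood glucose fluctuation pattern to explore prediction of diabetes risk or glucose levels", and it goes on to name monitoring of glycemia after the meal.

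**Data.** According to Results, "Eight photoplethysmography recordings per participant were collected across 4 mealtime points using 2 wearable devices". Capillary glucose was measured at all four points, and plasma glucose only at fasting and 2 h (Table 1).

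**Accuracy.** Statistical Analysis states: "The accuracy of the prediction model will be analyzed using both Type I and Type II Parkes Error Grids". It describes the unit of that measure: "Each device reading is compared with a reference value and placed into 1 of 5 zones". The other performance measures are the AUC, sensitivity, specificity and the F1-"score of the BGEM model will also be evaluated and presented". All of these are classification measures. Study Design adds an aim to assess measurement error separately in men and women with and without diabetes, sized by the Bland-Altman method.

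**Repeated measurements.** Statistical Analysis plans profile analysis, regression and mixed models of blood sugar profiles, "taking into consideration the correlation between the repeated measurements within each individual". It does not say that predicted change is compared with measured change.

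**Inputs.** Non-Photoplethysmography Data Preprocessing lists seven inputs that do not come from the optical signal. Diabetes status and meal timing are among them.

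**The concern.** Monitoring means following one person's glucose as it rises and falls. A measure that scores each reading alone gives credit for three different things: knowing that a person tends to run high, knowing that glucose is usually higher an hour after a meal, and detecting that this person's glucose rose more or less than expected. Only the third is tracking of an individual.

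The first two are available to this model without any optical information, because diabetes status and meal timing are inputs and the sample is split between 473 people with and 412 without diabetes. A favourable grid therefore cannot be attributed to tracking. At stake is a statement that the wearable is suitable for monitoring, supported by a result that a table of group means by meal time might also produce.

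**Working it through.** **1. The plan's own figure.** Study Design gives 200 per group for a 95% CI of ±0.24 SD. The Bland-Altman half-width for a limit of agreement is 1.96 × √(3/n) × SD. With n = 200 this is 1.96 × √0.015 = 0.240 SD. Four groups give 800, and 800 / 0.90 = 889, against about 890 planned. The figure reproduces and is not in dispute. It concerns the precision of agreement between single readings, not change within a person.

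**2. Each stated measure set against the goal.**
- Parkes grid: one predicted and one measured value per point. Splitting the grid by diabetes group or time point would not alter this.
- Measurement error in four groups: removes the difference in level between groups. Spread of level within a group remains, and change is still not assessed.
- AUC, sensitivity, specificity, F1: classification.
- Four-point time series (Model Training): an input to the model, not a measure of accuracy.
- Profile analysis and mixed models: not said to set predicted change against measured change.

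**3. A ceiling for a predictor that tracks nothing.** Let b be the share of total glucose variance that lies between persons. A predictor equal to each person's own mean has correlation √b with measured glucose over all readings. The article does not give b. For an assumed 50% to 80%, √0.5 = 0.71 and √0.8 = 0.89. This is an upper bound only: the mean of a held-out person is not known exactly. Correlation is also not one of the plan's measures. The predicted change is constant, so its correlation with measured change is undefined.

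**4. Illustration with predictors that need less.** A simulation of 885 people (473 with diabetes) at four time points. All glucose values are assumed. Low, mid and high scenarios for the meal rise:
- fasting mean (SD) without diabetes, mg/dL: 92 (9), 92 (9), 95 (10)
- fasting mean (SD) with diabetes, mg/dL: 140 (40), 150 (50), 150 (50)
- typical peak rise without / with diabetes, mg/dL: 30/60, 40/80, 55/110
- rise at 1, 2 and 3 h in the ratio 1 : 0.75 : 0.35, its size varying between people
- random error per reading: 6%, 7%, 8%

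The article does not give the grid boundaries, so bands of ±20% and ±40% relative error stand in for zones.

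| Predictor (low / mid / high) | r, all readings | within ±20% | within ±40% |
|---|---|---|---|
| Person's exact mean (ceiling) | 0.90 / 0.89 / 0.84 | 85 / 76 / 65% | 98 / 95 / 91% |
| Diabetes status only, flat | 0.65 / 0.64 / 0.60 | 64 / 57 / 51% | 89 / 86 / 82% |
| Diabetes status and meal time | 0.75 / 0.75 / 0.77 | 72 / 68 / 66% | 92 / 90 / 89% |

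The between-person share in these scenarios was 0.81, 0.79 and 0.70. The third row uses no optical signal and gives everyone in a group the same curve. Yet its correlation with measured deviations from each person's own mean, over all four times together, was 0.86 / 0.86 / 0.87. A within-person measure that leaves the average curve in would therefore also be passed without individual tracking.

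**5. Data for a direct test.** One participant missed the fourth measurement (Photoplethysmography Data Preprocessing): 885 × 3 − 1 = 2,654 changes from fasting per device. The time-series model excludes that participant: 884 × 3 = 2,652.

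**The case against.** Several points on the other side carry weight.

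- *This is a condensed article, and a fuller plan may hold a within-person measure.* That is possible. But the article does name its accuracy measure, and the point is that this measure does not match a stated goal. It is not a complaint about detail left out.
- *The goal is modest.* Model Training speaks of an intention to "explore prediction of diabetes risk or glucose levels and probable glycemia monitoring post meal", and the main aim is to collect a training dataset. A reader might infer that the monitoring goal will be declared met or not met on the grid. The article states no threshold or decision rule, so that inference is not supported.
- *Pooling is not in the text.* A reader might infer one grid over all participants. The article does not say how grids are grouped, and Study Design plans four groups separately for measurement error. The point does not need pooling, since any such grid still scores readings one at a time.
- *The repeated measurements are used.* They are, as model input and in the mixed models. It would also be too strong to say that those analyses exclude predicted values: the text says only blood sugar profiles, and the Abstract's Conclusions link profiles to evaluating the model. The article leaves this open.
- *The grid does penalise missed excursions.* In part. In the illustration even the exact-mean predictor falls from 85% to 65% within ±20% as the meal rise grows, and diabetes status alone reaches only 51% to 64%. The measures are not blind to poor tracking; they cannot separate it from level and average curve.
- *The 0.71 to 0.89 range overstates matters.* As evidence of what this model would score, it does. It stands only as a ceiling.

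**Conclusion.** The concern holds in this form: for predicted glucose, every stated performance measure can look acceptable when no individual's excursion is tracked, although monitoring after a meal is a stated goal and four readings per person are on hand to test it. This rests on the text alone: the per-reading description of the grid, the single-reading nature of the measurement-error aim, and the presence of diabetes status and meal timing among the inputs.

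The size is not known. With assumed glucose values and relative-error bands in place of grid zones, a lookup on diabetes status and meal time placed 66% to 72% of readings within ±20% and 89% to 92% within ±40%. These figures show direction and plausible extent; they do not predict the trial's result. Nor does the point imply that the optical signal fails to track glucose, only that the measures as stated would not reveal whether it does.

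**What to change.** Add to Statistical Analysis, as the accuracy measure for monitoring:

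- In held-out participants and for each device, compare predicted with measured capillary change from the person's own fasting value. Capillary glucose is the suitable reference because it exists at all four time points.
- Do this separately at 1, 2 and 3 h and within the groups with and without diabetes, so that neither the average meal curve nor the group level contributes.
- Report correlation, calibration slope and error.
- Set the result against the same model fitted with only the non-photoplethysmography features. This benchmark is needed because fixed characteristics such as age or weight may predict the size of the rise within a group, and stratifying does not remove that.
- Base any statement about monitoring on this comparison, and keep the Parkes grids as the measure of point accuracy.

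The cost is a little more analysis of data already held, including one further model fit per device without the optical features. The figure may be less favourable than the grid.

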## Results

The IRB approval was given on July 15, 2024, after which the data collection was started on July 30, 2024, and finished on October 5, 2024; the analysis was projected to be concluded in the third quarter of 2025 and the results submitted for publication at the end of 2025.

A total of 885 participants (473 with diabetes and 412 without diabetes) were enrolled. Eight photoplethysmography recordings per participant were collected across 4 mealtime points using 2 wearable devices. Participants completed the International Physical Activity Questionnaire (IPAQ) long form and additional questionnaires on diabetes and related risk factors. Capillary and plasma blood tests were performed, and results were recorded.

## Discussion

### Overview

This study will provide more data to further empower the BGEM AI model that has been developed since 2022 [12].

Photoplethysmography feature data from participants, collected across 4 time points, are intended to support the improvement of model performance across diverse racial groups, risk factors, and skin types in terms of its accuracy and robustness. The study design also addresses issues that have been reported to influence photoplethysmography sensors, such as motion artifacts.

The inclusion of additional clinical data such as anthropometric measurement, HbA_1c_, hematocrit, and other blood parameters performed in this study will give a more expansive view on factors that may influence photoplethysmography blood glucose predictive ability [14-16,28]. Analysis of these factors will provide insight into whether any of them influence BGEM accuracy or can be used as additional data to improve its performance.

This study is the first to report performance of photoplethysmography-based AI model used in the Indonesian population. Population-wide DM screening in Indonesia posed a problem to any health intervention program due to the challenging geography and population spread across multiple islands and diverse ethnicity of Indonesian people [29,30]. Therefore, this study can become a foundation of BGEM use in DM management, prevention, and screening in Indonesia.

DM, with its huge disease burden and increasing number of afflicted populations, needs new, innovative, and effective means to control and minimize its impact [31,32]. This protocol paper hopes to provide a base method in developing a noninvasive photoplethysmography-based AI model to predict blood glucose level and evaluating DM status of the subject.

### Comparison With Previous Work

BGEM use in the relatively large Indonesian population is unique and will become an important stepping stone for developing a noninvasive model that is effective in blood glucose screening and monitoring and DM management. The previous study of BGEM was performed in a female-dominant and mainly non-DM population [13]; thus, this study with a different gender make-up and larger DM population (Table 3) will give a good contrast and data set with different population characteristics that may increase the model performance and generalizability [12,28].

**Table 3. T3:** Comparison of basic population characteristics between the previous clinical study at KK Women’s Hospital, Singapore, and the current study in Krida Wacana Christian University (Ukrida) Hospital, Indonesia.

Characteristics	KK Women’s Hospital	Ukrida Hospital
Age (y), mean (SD)	38.73 (10.60)	44.22 (11.79)
Female proportion, n/N (%)	436/500 (90.3)	535/885 (60.45)
BMI (kg/m^2^), mean (SD)	24.4 (5.13)	26.77 (5.08)
Type 2 DM^a^ proportion, n/N (%)	157/500 (31.40)	473/885 (53.44)

a DM: diabetes mellitus.

The study has a comprehensive 4 time points of data collection, which is more extensive [33,34], and will provide a more complete view of how blood glucose level fluctuates between different state of food intake. The additional 1 and 3 hours after the meal may give a clearer view of blood glucose level changes compared to the standard fasting and 2-hour postmeal that is already widely accepted. Additionally, the use of AI in assessing glycemic variability is very limited [35], and to our knowledge, no study using photoplethysmography-based sensors has been reported despite its strong potential use for DM management. Therefore, this study will also be giving new and novel insight on the topic.

### Study Limitations

 This protocol has certain limitations. We prioritized achieving a balanced distribution of gender and participants with and without diabetes. With this focus, efforts were made to increase the overall number of participants. As the sample size grew, a broader range of demographic characteristics was naturally captured, reflecting the inherent diversity of the larger Indonesian population. However, no deliberate strategies were employed to design or randomize demographic features; the observed diversity emerged organically from the expanded participant pool. Several demographic features, such as participants aged over 60, are underrepresented; this will undermine the understanding of photoplethysmography in BGEM’s predictive ability in elderly population. Although the study includes a diverse range of ethnicities, the overall ethnic composition does not reflect the general proportions of the Indonesian population. This limits the extent to which certain inferences can be drawn from the final data analysis. Future studies with more proportional sampling from the general Indonesian population should address this bias.

### Conclusions

This protocol paper outlines the methodology designed for evaluating BGEM, a photoplethysmography-based AI model designed to estimate blood glucose levels and diabetic risk. The clinical trial was conducted on Indonesian participants with and without DM, while considering various influencing factors. The protocol is distinctive as it aims to generate high-quality training data for the AI model, ensuring balanced data structure, sufficient data quantity, diversity, and comprehensive relevant information including unique data on glycemic variability using wearables for downstream analysis and future research.
